### Incentives and compensation

Participants who participate in the study will receive an incentive totaling to 14.48 USD (100 RMB). During the testing period, the HCV screening test (serum anti-HCV antibody) will be reimbursed to participants in either study arm, after the participant completes the follow-up survey and the research team confirms the testing records. Reimbursements will cover up to 4 USD (28 RMB) of testing costs for HCV. The participant will receive reimbursement only if the demographic information on the test results matches the participant’s self-reported information, and the date of testing falls within the intervention period.

### Monitoring

A researcher will check each survey for completion and internal consistency. Each participant’s baseline and follow-up survey and test report will be checked for consistency of their verified cell phone number and demographic information. Test results must be confirmed by testing records at HKU-SZH or verified based on participant socio-demographics as reported in their baseline survey. A telephone number and WeChat account managed by the research team will be made available to participants for any questions or concerns that may come up during the study.

### Data analysis

#### Primary analysis

Participant baseline characteristics will be summarized using descriptive analyses. The primary analysis will evaluate whether the crowdsourced internet-based intervention package is superior to standard-of-care in increasing HCV testing uptake among the general public and target populations in China. The effect of the intervention on HCV testing uptake will be evaluated first using an intention to treat analysis that includes participants lost to follow-up. The proportion of participants with confirmed HCV testing in the intervention and control arms will be calculated separately using a 95% binomial proportion confidence interval (CI). The proportion of testing uptake between intervention and control arms will be compared using chi square test. Logistic regression adjusted with potential confounders will be applied to confirm the effect of intervention on the outcomes. Moreover, multiple logistic regression will be conducted to evaluate the effect of the following baseline factors on HCV testing uptake: previous health care service utilization behavior; trust in physicians and the health care system; knowledge of and access to healthcare services; membership in groups at high risk for HCV.

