### Sample size

The anti-HCV seroprevalence in China is estimated to be between 2.2 to 3.7%, giving an average of 3% prevalence of anti-HCV in the recruited population [21, 22]. The testing rate of conventional public health marketing methods (messages created by public health professionals) is approximately 35% [14]. If we conservatively assume crowdsourcing improves testing rates by 10%, together with 90% power and an alpha risk of 5%, a sample size of 1006 patients (*n* = 503 in each arm) will be required.

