### Randomization and allocation

Once they have signed the consent form, participants will be randomly allocated on a 1:1 ratio to either the intervention or control group through a randomization procedure using permuted blocks. SAS software (Cary, North Carolina, USA) will be used to create the allocation sequence using PROC PLAN and RANUNI functions. Participants will be allocated sequentially in the order in which they are enrolled. This study will be not be blinded, since participants will know their randomization assignment based on whether they receive the intervention, and investigators will be aware of the randomization assignment.

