### Data collection and measures

Pre-intervention and post-intervention surveys will be delivered to the participants’ mobile devices and completed using Survey Star^@^ (Wechat, China), a web-based survey platform that meets industry standards for security and functionality. Both surveys were written in Chinese and verified for clarity and cultural appropriateness with 13 Chinese individuals in Guangdong province, including both genders and ages groups.

Recruited individuals will first be assessed for eligibility by the researcher. Eligible participants will then be asked to complete the baseline survey on Survey Star^@^. The baseline survey will include the following domains: sociodemographic characteristics, including migrant status; access to healthcare at HKU-SZH; trust in healthcare providers; knowledge of and attitudes towards HCV; and risk of contracting HCV. Migrant status will be defined based on the definition of internal migrant from the National Bureau of Statistics of China [23]. Trust in healthcare providers will be assessed using three items previously used to measure provider trust in young Chinese men [15]. Stigma towards HCV will be assessed using a combination of items adapted from the Toronto. Risk of contracting HCV was assessed using 8 items typically used by HKU-SZH providers for assessing HCV risk.

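### The primary comparison is a valid but unadjusted chi-square test; a pre-named, covariate-adjusted comparison would use baseline data already collected, for a modest gain in precision

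*Protocol article*

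**What the plan says.** The Primary analysis section of the protocol article sets out three steps for the primary outcome, confirmed HCV testing within four weeks:

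- The between-arm comparison: "The proportion of testing uptake between intervention and control arms will be compared using chi square test".
- A supporting model: "Logistic regression adjusted with potential confounders will be applied to confirm the effect of intervention on the outcomes". The article does not say which variables these are.
- A separate multiple logistic regression of testing uptake on four groups of baseline factors: earlier use of health services, trust in physicians and the health system, knowledge of and access to healthcare services, and membership of a high-risk group. The article does not say that these are also the adjustment set.

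The section on data collection shows that related information is gathered at baseline: "The baseline survey will include the following domains: sociodemographic characteristics, including migrant status; access to healthcare at HKU-SZH; trust in healthcare providers", together with knowledge of and attitudes to HCV, and HCV risk. The section on randomization describes 1:1 allocation in permuted blocks after consent, without blinding: "investigators will be aware of the randomization assignment".

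**The concern.** Two choices stated in the article could be better.

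**Unused information.** The plan intends to study several baseline factors as possible determinants of testing, yet it leaves them out of the comparison that decides the trial. If they do predict testing, adjusting for them gives a more precise treatment comparison from the same participants. The chi-square gives up that precision and saves nothing in data collection.

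**The criterion for adjustment.** Randomisation removes systematic confounding by baseline factors, so confounding is not a useful guide to what belongs in the model. Prognostic value is. A set described by confounding points towards chance imbalance as the reason for including a variable.

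A smaller, related matter is the scale of the supporting result. The odds ratio from a logistic model that holds covariates fixed is a different quantity from the crude odds ratio, even when the arms are perfectly balanced. The two will differ somewhat for reasons unrelated to strength of evidence, which makes the adjusted odds ratio an awkward check on a comparison of proportions.

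**Working it through.** **Inputs from the Sample size section**

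- Comparator rate, in per cent: "The testing rate of conventional public health marketing methods (messages created by public health professionals) is approximately 35".
- Improvement, in per cent: "If we conservatively assume crowdsourcing improves testing rates by 10". I read this as absolute, 35% v 45%, because that reading reproduces the stated total. A relative 10% (35% v 38.5%) would need 3,986 per arm.
- Error rates: "together with 90% power and an alpha risk of 5" per cent. Sidedness is not stated; two-sided reproduces the total.
- Total: "a sample size of 1006 patients", 503 per arm.

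**Input not in the documents:** R², the share of outcome variance that the baseline covariates explain. Assumed range 0.02 to 0.20.

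**Step 1. Reproduce the plan's figure.** For an unadjusted two-sided test of two proportions, without continuity correction,

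n per arm = [1.960·√(2·0.40·0.60) + 1.2816·√(0.35·0.65 + 0.45·0.55)]² / 0.10²

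= [1.960·0.6928 + 1.2816·0.6892]² / 0.01 = (1.3579 + 0.8832)² / 0.01 ≈ 502.3, rounded up to **503 per arm, 1006 in total**.

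This matches exactly. Power at 503 per arm is Φ[(0.10·√503 − 1.3579)/0.6892] = Φ(1.284) = 90.0%. The planned test meets its own target.

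**Step 2. Value of adjustment.** Adjusting for covariates that explain a share R² of the outcome variance reduces the variance of the difference in proportions by about the factor (1 − R²). That is equivalent to 503/(1 − R²) participants per arm in the same power formula. The 95% CI half-width is 1.96·√[(0.2275 + 0.2475)·(1 − R²)/503].

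| Assumed R² | Equivalent n per arm | Power | CI half-width (points) | Narrowing, 1 − √(1 − R²) |
|---|---|---|---|---|
| 0 (chi-square) | 503.0 | 90.0% | 6.0 | – |
| 0.02 | 513.3 | 90.6% | 6.0 | 1.0% |
| 0.05 | 529.5 | 91.4% | 5.9 | 2.5% |
| 0.10 | 558.9 | 92.8% | 5.7 | 5.1% |
| 0.15 | 591.8 | 94.1% | 5.6 | 7.8% |
| 0.20 | 628.8 | 95.2% | 5.4 | 10.6% |

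A separate simulation of the covariate-adjusted logistic test (503 per arm, five independent covariates with equal coefficients, 4,000 trials per setting) gave power of 91.5%, 92.7% and 93.9% at R² of 0.05, 0.10 and 0.15, in line with the table.

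**Step 3. Crude and adjusted odds ratios under perfect balance.** Crude: (0.45/0.55)/(0.35/0.65) = 0.818/0.538 = 1.52. Holding the marginal rates at 35% and 45% and integrating over a normally distributed covariate score, the conditional odds ratio is about 1.55, 1.59 and 1.64 at R² of 0.05, 0.10 and 0.15. The evidence has not changed; only the quantity being estimated has. Averaging the model's predictions over all randomised participants returns to the difference in proportions that the chi-square addresses.

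**The case against.** The strongest reply is that nothing here is an error. A chi-square test is valid under 1:1 randomisation, it is fixed as the comparison, and it is the test on which the sample size was built. An unadjusted primary analysis with an adjusted supporting model is a common structure. This stands, and it limits the point to efficiency and interpretation.

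The gain is also small and its size unknown. At R² of 0.02 it is 0.6 of a percentage point of power. Factors such as access, trust and knowledge may overlap, so together they may explain less than their number suggests. The article proposes to evaluate these factors and does not assert that they predict testing. All of this stands, which is why the result is given as a range.

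A reader might go further and infer that the trial's 5% error rate is at risk, because investigators know the assignment and could pick covariates to suit. Simulations under no effect show what unrestricted picking could do in the worst case: 7.1% to 9.2% false positives when any significant result among 16 subsets of four covariates is accepted, and about 10% with 32 subsets of five, against about 5% for a fixed set. The documents do not support that inference. They nowhere say that covariates will be chosen by imbalance, by result or after seeing data by arm. A covariate list may properly sit in the analysis plan, which is not shown. Any such selection would affect only the supporting adjusted result and would leave the chi-square at its nominal level.

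Nor does the article claim that a larger adjusted odds ratio counts as confirmation. Step 3 is a reason to report on the scale of proportions, not a charge against the text.

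**Conclusion.** The point holds as a matter of efficiency. The plan fixes an unadjusted primary comparison that is valid and adequately powered on its own assumptions, and it leaves unused baseline information that it already collects. Its stated criterion for adjustment, confounding, is the wrong one for a randomised trial.

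The precision forgone is modest: 0.6 to 5.2 percentage points of power, or a confidence interval about 1% to 11% wider than it could be. This rests on 35% v 45%, on 503 per arm and on an assumed R² of 0.02 to 0.20 that the documents neither give nor exclude. Neither the validity of the primary test nor its 5% error rate is in question.

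**What to change.** - Make the primary comparison a logistic regression of confirmed testing on arm plus a short prognostic set, named before any data are seen by arm. Candidates are age, sex, migrant status and the four groups already listed in the Primary analysis section: previous service use, trust, knowledge of and access to healthcare services, and high-risk group.
- Use only values recorded before allocation. The article places randomisation after consent and describes the survey as pre-intervention, but it does not clearly order the survey and the allocation. In an unblinded trial, answers given once the arm is known are not safe covariates.
- Average the model's predictions over all randomised participants and report the standardised difference in proportions with its 95% CI.
- Keep the chi-square as the supporting analysis, and replace the reference to potential confounders with the named set.
- Fill missing baseline values simply (mean or a missing category), so that nobody is dropped for a missing covariate.

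The cost is one paragraph of analysis wording and a little programming, with no new data. The small downside is that the primary result then rests on a working model, which is why the chi-square stays as a check.

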#### Missing data plan

Any participants lost to follow-up will be included. If an outcome is missing for < 15% of participants, analyses will use a complete-case approach. If an outcome is missing for ≥15% of participants, analyses will use multiple imputation.

#### Secondary analyses

Participants in the control and intervention arms will also be compared for differences in proportion of participants achieving secondary outcomes: number requiring referral for HCV confirmatory testing; number that receive confirmed diagnosis for HCV; number that attend follow-up visits at HKU-SZH for HCV treatment; number that achieve HCV cure.

## Discussion

Historically, HCV prevalence in China has been low, yet data suggests that that the HCV prevalence in China is rising across age groups [5, 24]. This may be attributed to that HCV currently does not have a preventive vaccine, and there is poor public awareness of the virus. As such, the HCV care continuum in China should be addressed urgently. However, according to a recent systematic review, few studies have evaluated interventions to increase HCV testing or treatment uptake [25]. Additionally, prior studies have targeted special populations such as people who use drugs (PWUD) and MSM, and have been limited to high risk group in high-income countries [25]. Few controlled trials have been conducted among the general population in low- or middle-income countries with high prevalence of viral hepatitis.

Our study is the first to utilize crowdsourcing for viral hepatitis testing and linkage-to-care in a general population. Our study be conducted in context of the new and evolving primary care system in China, a middle-income country that is endemic for HCV, but where public and professional knowledge about HCV is limited. The findings will contribute significantly to the existing literature on viral hepatitis testing in the primary care setting.

Crowdsourced images promoted through social media platforms have demonstrated efficacy for increasing HIV screening and condom use while simultaneously increasing community engagement and knowledge about the respective issue [11, 12]. Crowdsourcing also has the potential to address sensitive issues associated with marginalized populations such as MSM [13]. However, despite the high rate of social media and technology use China crowdsourcing may have limited reach to certain individuals. These overlooked individuals are likely to be part of the vulnerable population such as PWUD or people with mental health disorders, or older people with low technological literacy or social media use. Since the participation in our study requires the use of a smartphone and knowledge of social media, the study will exclude those who do not use these services. The recruitment of the targeted study population based on an establishing hospital setting would form a limitation as participants would have been engaged in medical care or specific treatment. Individuals who are distrustful of or disengaged from medical care are less likely to be recruited. Finally, our study does not directly address the lack of primary provider training in China’s HCV care continuum [9].

The findings from this study can still inform future decisions and policies to improve HCV care training for primary care providers in China and shape the future role of China’s primary care system in public health campaigns.

## Data Availability

Currently not available as the trial is still in progress. Future data from this trial can be obtained from the corresponding author on reasonable request.

## Abbreviations

HCV: Hepatitis C virus
HIV: Human immunodeficiency virus
STI: Sexually transmitted infections
HKU-SZH: University of Hong Kong-Shenzhen Hospital
FMPC: Department of family medicine and primary care
RCT: Randomized controlled trial
WHO: World health organization
SVR: Sustained virological response
PWUD: People who use drugs
MSM: Men who have sex with men
